## Abstract

**Background:**

Cerebral cavernous malformations (CCMs) are vascular malformations characterized by clusters of enlarged leaky capillaries in the central nervous system. They may result in intracranial haemorrhage, epileptic seizure(s), or focal neurological deficits, and potentially lead to severe disability. Globally, CCMs represent the second most common intracranial vascular malformation in humans, and their familial form (FCCMs) accounts for one-fifth of cases. Neurosurgical excision, and perhaps stereotactic radiosurgery, is the only available therapeutic option. Case reports suggest that propranolol might modify disease progression.

**Methods:**

Treat_CCM is a prospective, randomized, open-label, blinded endpoint (PROBE), parallel-group trial involving six Italian clinical centres with central reading of brain magnetic resonance imaging (MRI) and adverse events. Patients with symptomatic FCCMs are randomized (2:1 ratio) either to propranolol (40–80 mg twice daily) in addition to standard care or to standard care alone (i.e. anti-epileptic drugs or headache treatments). The primary outcome is intracranial haemorrhage or focal neurological deficit attributable to CCMs. The secondary outcomes are MRI changes over time (i.e. de novo CCM lesions, CCM size and signal characteristics, iron deposition, and vascular leakage as assessed by quantitative susceptibility mapping and dynamic contrast enhanced permeability), disability, health-related quality of life, depression severity, and anxiety (SF-36, BDI-II, State-Trait Anxiety Inventory).

**Discussion:**

Treat_CCM will evaluate the safety and efficacy of propranolol for CCMs following promising case reports in a randomized controlled trial. The direction of effect on the primary outcome and the consistency of effects on the secondary outcomes (even if none of them yield statistically significant differences) of this external pilot study may lead to a larger sample size in a definitive phase 2 trial.

**Trial registration:**

ClinicalTrails.gov, NCT03589014. Retrospectively registered on 17 July 2018.

## Background and rationale

Cerebral cavernous malformations (CCMs) are vascular lesions consisting of clusters of abnormally dilated blood vessels (capillaries). These lesions are mainly located in the central nervous system (brain and spinal cord) and, more rarely, affect the skin and retina. CCMs have typical raspberry-like appearance due to their composition of multiple bubble-like structures called caverns. Each cavern is filled with blood and lined by a layer of endothelial cells. In the case of CCMs, the bubble-like caverns are grossly dilated vessels that leak due to defects in the endothelial cells and due to the loss of other structural components that are required for vessel wall integrity. Lesion size is variable, ranging from microscopic to a few inches in diameter. Subjects may be asymptomatic or present a wide variety of symptoms including seizures, intracranial haemorrhages, or focal neurological deficits [1–3].

The CCM prevalence is approximately one out of every 500–600 people. However, such an estimation strongly depends on the methodology of ascertainment. Autopsy studies indicate the prevalence of CCMs to be between 0.2% and 0.5% of the population, while papers using brain MRI clinical series report a prevalence between 0.39% and 0.9% [4–6].

CCMs occur in sporadic or familial (FCCM) forms. Multiple lesions are more common in FCCMs and the number of lesions is strongly correlated with the patient’s age. The diagnosis of FCCMs is established with the presence of either or both of the following: multiple CCMs, and multiple family members with one or more CCM. The identification of a heterozygous germline, pathogenic variant in *KRIT1*, *CCM2*, or *PDCD10* confirms the diagnosis of FCCMs [7]. Genetic screening is positive in 96% of families with multiple affected members, and in 57% of sporadic cases with multiple lesions (more so if new lesions form over time) [2]. While FCCM patients bear ubiquitous germline heterozygous mutation of CCM genes, the analysis of the surgically removed cavernomas discloses a second somatic mutation in the same CCM gene. This suggests that local genetic homozygosity is indispensable to prime the pathogenic cascade. The analysis of affected tissues often discloses a second somatic mutation, which is likely indispensable to prime the pathogenetic cascade, suggesting a two-hit mechanism [8–10]. The prevalence of FCCMs, highly variable among different populations and case series, ranges from 0.2 to 3/10,000 subjects [11, 12]. Multiple CCMs, suggesting FCCMs, affect roughly one-fifth of people with CCMs [1]. Nonetheless, these new findings on genetic determinants have not impacted on actual treatment of CCMs.

Although the presentation of CCMs is not uncommon in children, individuals often show the first sign of symptoms in their 20s or 30s. Globally, the annual bleeding rate is 2.5% per patient-year, with prior haemorrhage and brain stem location being the major risk factors for CCMs to bleed [1, 13].

CCM is an endothelial disease as demonstrated in murine models. In fact, only mice with endothelial-selective inducible ablation of FCCM genes develop cerebral vascular malformations with morphological and molecular features similar to humans [14–16]. The activity of the three members of the complex, encoded by the three FCCM-related genes, has to converge in the same pathway, since the morphology and specific brain localization of the vascular malformations is roughly comparable in the three genetic forms of FCCM.

No pharmacological treatment is at present available to inhibit the formation of new malformations, to stabilize the existing ones and stop their progression. To date, the standard of care is represented by treatment of CCM-associated clinical manifestations, such as headache and epilepsy, and consists of anti-epileptic drugs or drugs for recurrent headache [17]. The only available treatments are neurosurgical excision or stereotactic radiosurgery. Surgical removal of lesions associated with intractable seizures or focal deficits from recurrent haemorrhage or mass effect may be considered [13, 18, 19], with at times significant complications [20]. Neither neurosurgery nor radiosurgery can completely eradicate the multiple lesions of FCCMs, which increase in number over time. Thus, pharmacological therapies are urgently needed, particularly in FCCMs.

Propranolol has efficacy, documented in RCTs, for the treatment of infantile haemangiomas, another common vascular lesion affecting the skin [21–24]. To date, only anecdotal reports have been published supporting its efficacy in CCMs [19, 25–27]. In mice, propranolol was effective in preventing CCM expansion and in reducing vascular permeability ([name] et al., 2019, unpublished data).

The recognized safety of propranolol, as demonstrated by millions of patients of all ages, including children treated over the last 40 years [28], makes this drug a good candidate for a pragmatic, external, pilot randomized trial.

## Methods/design

### Aims

The purpose of this exploratory pilot trial is to test whether 2-year treatment with propranolol in addition to standard care can reduce the incidence of clinical events, as compared to standard care in patients with FCCMs. Furthermore, this trial will help to set up future clinical trials in an area where there is to date no approved drug reducing the progression of CCM lesions, and will pave the way to study the mechanisms underlying the possible therapeutic role of propranolol in CCMs.

### Design

The study protocol was designed according to the real-life management of patients with FCCMs (Fig. 1). Treat_CCM is a multicentre, open-label, randomized controlled trial (PROBE design, prospective randomized open trial with blinded evaluation of outcomes) in patients with FCCMs. Patients, fully informed of the trial, after signing the informed consent form are randomly assigned by computer, upon completing the randomization electronic case report form (e-CRF), in a 2:1 ratio to the study groups: one receiving *propranolol* in addition to standard care; the other, *controls*, receiving standard care alone (Fig. 1). The study will be open-label since the implementation of blinding would require placebo and ad hoc procedures with costs non-sustainable in a pilot study fully supported by public funding. In order to reduce possible biases, a PROBE design will be applied so that each MRI examination will be centrally read after de-identification, and all adverse clinical events will be centrally adjudicated. It should be pointed out that by no means will surgery, whenever indicated, be delayed and/or avoided because of study treatment allocation.

**Fig. 1 Fig1:**
[figure not shown]
Study flow chart. bid twice daily, CCM cerebral cavernous malformation

A two-step trial [29] is proposed as follows:
Step 1: duration 2 years; 60 patients, 40 in propranolol group and 20 controls; if no difference between the study groups in 2-year incidence of adverse clinical events (e.g. intracerebral haemorrhage (ICH) or focal neurological deficits (FND)) is found and different MRI variables suggest improvement, the second phase is started, to assess long-term efficacy of propranolol.Step 2: single-arm study, all patients in the propranolol group; the drug will be declared effective in the case that the patients’ condition is improved or remains stable over the 2-year follow-up (e.g. years 3 and 4). The threshold of proportion of responses will be defined upon analysis of the 2-year follow-up data.

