### Sample size

To the best of the available knowledge, the 2-year risk of CCM-related events (ICH and FND) was estimated at 10.1% in CCM patients receiving recommended standard care [1]. Upon performing a formal sample size calculation, 834 patients should be included in the study to demonstrate a risk reduction of 50% with a power of 80% at a significance level of one-tailed α = 0.05. This estimate is unrealistic both for the over-optimistic treatment effect size and for the number of patients to be included, incompatible with a rare disease.

Therefore, in order to obtain preliminary data, a pilot study is planned, adopting a confidence interval approach, rather than using the more usual power and statistical significance method [40]. The sample size calculation for the pilot trial is driven by the proposed sample size of the main trial. According to the nature of the pilot study design, an 80% one-sided confidence interval is chosen, instead of the 95% two-sided interval usually considered for formal comparative trials. With 60 patients randomized in a 2:1 propranolol:control ratio, in the absence of a reduction of adverse events, a clinically meaningful effect, defined as ≥50% reduction of the 2-year risk of CCM-related events, can be excluded by the defined 80% upper confidence interval. Otherwise, the study will provide a promising signal of activity.

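### Step 2 would declare propranolol effective from an uncontrolled arm if patients improve or stay stable, with *stable* undefined and the pass mark left until the 2-year data are analysed

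*Protocol article*

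**What the plan says.** The scheme is in the protocol article under Methods/design, Design, in the two-step list below Fig. 1. Step 1 randomises 60 patients 2:1 for two years. Step 2 follows if clinical events do not differ between the groups and MRI variables suggest improvement.

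- **Step 2 design:** "Step 2: single-arm study, all patients in the propranolol group". No concurrent control remains. The wording fits either the 40 patients first allocated to propranolol or all 60 taking it.
- **Success rule:** "the drug will be declared effective in the case that the patients’ condition is improved or remains stable over the 2-year follow-up", where the period meant is years 3 and 4.
- **Pass mark:** "The threshold of proportion of responses will be defined upon analysis of the 2-year follow-up data".

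The Sample size section gives the background risk: "the 2-year risk of CCM-related events (ICH and FND) was estimated at 10.1% in CCM patients receiving recommended standard care". The effect of interest there is "a clinically meaningful effect, defined as ≥50% reduction of the 2-year risk of CCM-related events".

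Other sections set narrower limits. Statistical analyses says that inferential statistics cannot be done on the pilot data and that no formal hypothesis test is needed. The Discussion says that a trial of this size can at most reassure on safety and justify a later, adequately sized trial.

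**The concern.** The Step 2 sentence is a decision rule for efficacy, and it has three weaknesses.

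1. Staying stable counts as success. If most patients stay stable on standard care, the rule credits the drug with the natural course of the disease.
2. No control group is left against which to judge that course.
3. Neither the meaning of *stable* nor the pass mark is fixed in advance.

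Step 2 is also to start when Step 1 has found no difference in clinical events, so the declaration would not rest on a randomised clinical result.

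At stake is a published statement that propranolol works in a disease with no drug treatment. The Discussion itself warns that the drug may be prescribed off-label without clear evidence of benefit.

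**Working it through.** **Inputs from the article**
- 2-year risk of ICH or FND on standard care: 10.1% (Sample size).
- Effect of interest: risk halved, 10.1% to 5.05% (Sample size).
- Step 2 size: 40 or 60 (Design).

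**Assumptions**
- *Stable* means free of ICH and FND for two years.
- The 10.1% applies to this population.
- The pass marks are illustrative, because the article states none.

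**The article's own figure.** With control risk p1 = 0.101, propranolol risk p2 = 0.0505, one-sided 5%, 80% power, 2:1 allocation and unpooled variance:

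n(control) = [p1(1 − p1) + p2(1 − p2)/2] × (1.645 + 0.842)² / (p1 − p2)²
= (0.0908 + 0.0240) × 6.18 / 0.00255 ≈ 278.3, rounded up to 279.

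The total is 279 + 558 = 837, against the stated 834. The pooled formula with continuity correction gives 274 + 548 = 822. Both are within 1.5%, so the 10.1% is used consistently there.

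**Expected stability without the drug.** 1 − 0.101 = 0.899, about 36 of 40 or 54 of 60. With the risk halved it is 1 − 0.0505 = 0.9495.

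**Chance that an inert drug passes.** P(X ≥ r), with X binomial (n, 0.899):

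| Pass mark | n = 40 | n = 60 |
|---|---|---|
| 80% (32; 48) | 98.4% | 99.4% |
| 85% (34; 51) | 89.6% | 92.3% |
| 90% (36; 54) | 62.1% | 59.6% |
| 95% (38; 57) | 21.7% | 13.2% |

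**Strict marks.** Alpha is P(X ≥ r) at 0.899 and power is P(X ≥ r) at 0.9495:

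| Rule | Alpha | Power |
|---|---|---|
| 39 of 40 | 7.8% | 39% |
| 40 of 40 | 1.4% | 13% |
| 57 of 60 | 13.2% | 64% |
| 58 of 60 | 5.06% | 41% |
| 59 of 60 | 1.3% | 19% |

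For example, 40 of 40 has alpha 0.899^40 = 0.014 and power 0.9495^40 = 0.126. A one-sided level of at most 5% therefore needs 40 of 40 or 59 of 60.

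**Sensitivity to the background rate.** The Background states that "the annual bleeding rate is 2.5% per patient-year". Counting bleeding alone, 0.975² = 0.951 would be bleed-free at two years. An inert drug would then meet a 90% mark with probability 95.4% (n = 40) or 97.2% (n = 60).

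**The case against.** **The criterion may be wider than ICH and FND.** The rule speaks of the patients' condition, and MRI findings help trigger Step 2. The Background says that lesions in familial disease increase in number over time. If *stable* includes the MRI, fewer than 90% may be stable untreated, and the article gives no figure. This stands: the 90% is conditional. It does not rescue the rule, because an unknown untreated proportion is harder to judge a single arm against.

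**Setting a threshold from Step 1 is legitimate in itself.** This also stands. Step 1 data, including its 20 controls, may inform the planning of Step 2. The weakness is that no rule is stated for deriving the mark and that the same patients may supply both benchmark and test. The sentence can even be read as referring to the data of years 3 and 4, which would be worse.

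**A strict mark would solve it.** A reader might go to the other extreme and infer that a valid mark leaves almost no chance of success. That holds only at 5% one-sided, a level taken from the 834-patient calculation that the article sets aside. The pilot chose an 80% one-sided interval, which corresponds to a 20% level. At that level the marks are 39 of 40 and 57 of 60, with power 39% and 64%. Power is limited, but not negligible.

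**Withdrawn or operated patients.** A reader might infer that they drop out of the denominator. The article does not say so. Statistical analyses specifies intention to treat, and Guidelines for stopping treatment carries the last known status into the final analysis. What remains is narrower: a patient who was stable until surgery could be counted as stable.

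**The study calls itself exploratory, and Step 2 is conditional.** True, and Step 1 is unaffected. But neither statement withdraws the efficacy declaration, and an analysis plan that is not shown could define *stable* but could not add a control arm.

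**Conclusion.** The Step 2 rule is wrong as written: it can declare an inert drug effective, and it conflicts with the article's own limits on what the pilot can show. If *stable* means free of ICH and FND and the 10.1% applies, the chance of a false declaration runs from 98–99% at an 80% mark, through 60–62% at 90%, to 13–22% at 95%. These figures show the rule's behaviour over assumed marks; they do not predict the mark that the sponsor would choose. The 10.1% comes from CCM patients in general and may differ in symptomatic familial disease. The core conclusion needs neither assumption: without a concurrent control, improvement or stability in years 3 and 4 cannot be attributed to the drug.

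**What to change.** Replace the efficacy sentence with wording such as: *Step 2 is descriptive. It will report long-term safety, tolerability and the proportion of patients stable over years 3 and 4, with a confidence interval. Efficacy will not be declared from Step 2.*

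In the same amendment:
- Define *stable*, and any reference proportion, before Step 1 data are compared by arm. The first patient entered in March 2018, so nobody could have reached month 24 by the article's status date of end April 2019.
- If 89.9% is shown as a reference, label it as coming from CCM patients in general.
- State whether Step 2 means 40 or 60 patients.
- State how patients who are operated on or lost are counted.
- Leave efficacy to a future, adequately sized controlled trial. Step 1 can give a randomised estimate with its interval, but no confirmatory statement, since the article rules out inferential statistics on the pilot data.

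The cost is a wording amendment with no added patients or visits. The sponsor gives up an efficacy claim that the design cannot support.

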### Population

Eligible patients will be selected from the six participating clinical centres (Fondazione IRCCS Cà Granda Ospedale Maggiore Policlinico, Milan; Policlinico Universitario Agostino Gemelli, Rome; Fondazione IRCCS Istituto Neurologico Carlo Besta, Milan; Fondazione IRCCS Casa Sollievo della Sofferenza, San Giovanni Rotondo; IRCCS Centro Neurolesi “Bonino Pulejo”, Messina; ASST Grande Ospedale Metropolitano Niguarda Milan). In addition, other patients will be identified via CCM patient organizations, such as Associazione Nazionale Angioma Cavernoso Cerebrale ONLUS (https://www.anacc.net/). Inclusion and exclusion criteria are listed in Table 1.

**Table 1 Tab1:** Inclusion and exclusion criteria

Inclusion criteria	
1	Patients with familial cerebral cavernous malformations (FCCM)
2	History of clinical symptoms or events: ICH, seizures, stroke, permanent or transient focal deficits, intellectual disability, or any other neurological symptoms supposedly related to CCM
3	Age ≥18 years
4	Written informed consent to participate in the study prior to any study procedures
Exclusion criteria	
1	Implanted pacemaker or any other condition preventing the MRI examination
2	Bradycardia (< 50 bpm), second or third-degree AV block or symptomatic hypotension
3	Unstable diabetes
4	Severe asthma
5	Liver and/or renal failure
6	Current use of verapamil or diltiazem for risk of excessive bradycardia
7	Previous brain surgery (within 6 months)
8	Known hypersensitivity to study drug (propranolol or any of the ingredients)
9	Pregnant or lactating women, or women at risk of childbearing who are not under protection by an accepted method of contraception
10	Participation to another clinical trial
11	Inability to cooperate with the trial procedures
In addition to these specific exclusion criteria, all well-documented contraindications to beta-blocker use are also valid in this trial	

*AV* atrioventricular, *CCM* cerebral cavernous malformation, *ICH* intracerebral haemorrhage, *MRI* magnetic resonance imaging

### Intervention

Propranolol is a non-selective beta-blocker, indicated for the treatment of hypertension and other cardiovascular and neurological disorders. The recommended initial oral dose for the group randomized to propranolol is 40 mg twice daily, as recommended in Italian Pharmacopeia, to be up-titrated to 80 mg twice daily in the absence of excessive bradycardia (e.g. heart rate < 50 bpm) or hypotension. However, doses as low as 10 mg twice daily and up to 160 mg twice daily, 20–320 mg daily, are acceptable according to the individual’s tolerance of side effects. Both study groups will receive recommended standard care. Study treatment will be continued for the whole duration of the study.

### Outcomes

The primary endpoint will be the new occurrence of clinical symptomatic CCM-related events, which are intracerebral haemorrhage (ICH) and focal neurological deficits (FND), as defined by Al-Shahi Salman et al. [30], excluding seizures.

Secondary endpoints include the following:
Microvascular haemorrhages as assessed by MRI analysis of brain tissue magnetic susceptibility, a biophysical property proportional to the local iron content (susceptibility weighted imaging (SWI) and quantitative susceptibility mapping (QSM)), and dynamic contrast enhanced permeability (DCEP).Clinical outcomes, other than ICH and FND, such as global disability, health-related quality of life, depression severity, and two types of anxiety (state anxiety, or anxiety about an event, and trait anxiety, or anxiety personal level), as assessed by the SF-36, BDI-II and State-Trait Anxiety Inventory (STAI) questionnaires.Seizures.Different MRI CCM characteristics, such as location (cerebellum, brainstem, right/left hemispheric white matter, right/left basal ganglia), diameter, length, and MRI signal appearance. Lesions with previous surgical treatment will be excluded from imaging analysis.Appearance of de novo CCM lesions at MRI.

### Exploratory targets

#### Brain imaging

MRI is, at present, the objective non-invasive tool to track in vivo the evolution of CCMs. Recently, in vivo MRI assessment of iron deposition and vascular permeability with advanced MRI techniques, such as QSM and DCEP, have been proposed as objective and quantifiable biomarkers of disease activity in CCMs with potential application in natural history and clinical trials [31], expanding conventional imaging in cerebral cavernous malformations [32]. Iron leakage and vascular permeability have a central role in CCM pathogenesis and their quantification can be an objective biomarker of disease activity in CCMs. Therefore, the quantification of biomarkers of DCEP and QSM with in vivo MRI and their longitudinal changes may correlate with the clinical behaviour of CCMs [33]. Patients will undergo brain MRI at randomization and at 1 and 2 years of follow-up.

